## Abstract

**Background:**

Violence against adolescent girls in humanitarian settings is of urgent concern given their additional vulnerabilities to violence and unique health and well-being needs that have largely been overlooked by the humanitarian community. In order to understand what works to prevent violence against adolescent girls, a multi-component curriculum-based safe spaces program (Creating Opportunities through Mentorship, Parental involvement and Safe Spaces – COMPASS) will be implemented and evaluated. The objectives of this multi-country study are to understand the feasibility, acceptability and effectiveness of COMPASS programming to prevent violence against adolescent girls in diverse humanitarian settings.

**Methods/design:**

Two wait-listed cluster-randomized controlled trials are being implemented in conflict-affected communities in eastern Democratic Republic of Congo (N = 886 girls aged 10–14 years) and in refugee camps in western Ethiopia (N = 919 girls aged 13–19 years). The intervention consists of structured facilitated sessions delivered in safe spaces by young female mentors, caregiver discussion groups, capacity-building activities with service providers, and community engagement. In Ethiopia, the research centers on the overall impact of COMPASS compared to a wait-list group. In DRC, the research objective is to understand the incremental effectiveness of the caregiver component in addition to the other COMPASS activities as compared to a wait-list group. The primary outcome is change in sexual violence. Secondary outcomes include decreased physical and emotional abuse, reduced early marriage, improved gender norms, and positive interpersonal relationships, among others. Qualitative methodologies seek to understand girls’ perceptions of safety within their communities, key challenges they face, and to identify potential pathways of change.

**Discussion:**

These trials will add much needed evidence for the humanitarian community to meet the unique needs of adolescent girls and to promote their safety and well-being, as well as contributing to how multi-component empowerment programming for adolescent girls could be adapted across humanitarian settings.

**Trial registration:**

Clinical Trials NCT02384642 (Registered: 2/24/15) & NCT02506543 (Registered: 7/19/15).

## Background

Globally, approximately 59.5 million people were forcibly displaced in 2014 [1], which is one of the highest levels seen in decades. Throughout periods of armed conflict and displacement, women and girls face increased risk of violence due to a constellation of factors that may increase their vulnerabilities, such as weakened community protection mechanisms, existing inequitable and evolving gender norms, financial instability, limited economic opportunities, and separation from family members [2–4]. In fact, approximately one in five displaced women report experiencing sexual violence [5]. Intimate partner violence (IPV) and other forms of abuse or exploitation may also occur at higher frequencies and are of key concerns for conflict-affected women and girls [6, 7].

Within humanitarian emergencies, female adolescents aged 10–19 years are particularly at risk of sexual violence, sexual exploitation, and early marriage [2, 3, 8]. For example, the percentage of registered marriages which involved girls below age 18 doubled during two years of the Syrian conflict. This is thought to be due to a complex set of circumstances that families face in displacement which lead them to see marriage as the best option for gaining resources and supplies as well as protecting their daughters from violence outside the home [9, 10]. Adolescent pregnancy is also of concern for child brides within early and forced marriages. These young females may be expected and pressured to become pregnant as the result of inequitable gender norms and power dynamics, or due to the lack of access to contraceptive methods in emergencies, or pregnancy as the direct result of forced sex. [11, 12].

Not only do adolescent girls face increased vulnerability to violence, similar to development contexts, the needs of adolescent girls are often overlooked by communities, families, and service providers during and after conflict due to their lack of social status, stemming from gender inequalities and the invisibility of younger populations. Girls may also have limited mobility and therefore, face restricted access to pertinent life-saving information, schooling, and health and protection services [13, 14]. Limited understanding and investment to date by the humanitarian community of the specific factors that shape adolescent girls’ vulnerabilities and needs has led to inadequate resources and programming for this unique population [4, 15, 16].

Despite the multitude of reports on violence against women and girls in humanitarian settings and the damaging physical and mental health effects resulting from such violence, few rigorous studies have examined how best to prevent violence in such contexts [17, 18]. In fact, only two prevention studies focusing on reducing IPV in humanitarian settings have been completed to date, both of which only focused on adult women [19, 20]. Simultaneously, efforts in child protection research have demonstrated a small, but expanding evidence base for the use of safe spaces to support children’s psychosocial wellbeing in emergencies. The goals of such safe spaces, which can generally be constructed quickly in an emergency, are to provide children with a place to participate in activities and receive support to promote their overall well-being and resilience [21]. However, it remains unclear if safe space programming confers additional protection against the unique risks of violence that adolescent girls face [22, 23], particularly as most child friendly spaces do not have tailored programming by gender. Ultimately, while there are advances in IPV prevention strategies and child protection programming [19, 20], there is a glaring gap of rigorous evidence on how best to reduce violence against adolescent girls in emergencies.

To address this gap in the evidence, Columbia University and the International Rescue Committee (IRC), are undertaking an evaluation of the Creating Opportunities through Mentoring, Parental involvement, and Safe Spaces (COMPASS) program, of which a key strategy is to develop the skills and assets of girls with the support of female mentors in ‘safe spaces’, alongside additional engagement of caregivers and capacity-building of service providers. The objectives of this multi-country study are to understand the feasibility, acceptability and effectiveness of these approaches to respond to and prevent violence against adolescent girls in three diverse humanitarian settings.

## Methods

### Study design

Over three years (2014–2017), the COMPASS program is being implemented and evaluated in conflict-affected communities in the Democratic Republic of Congo (DRC), Sudanese refugee camps in Western Ethiopia, and in sites across Khyber Pakhtunkwa province in Pakistan, including Jalozai camp. In DRC and Ethiopia, the study design employs a wait-listed two-arm cluster randomized controlled trial. Given the exceedingly restrictive environment in Pakistan around issues of violence against girls, a mixed methods pre-post test is being implemented rather than an impact evaluation. Thus, the remainder of the study protocol manuscript will center on the trials taking place in DRC and Ethiopia. Further details of all study designs are found in Table 1. Qualitative inquiry will be used to complement the quantitative findings and to provide more nuanced understanding of processes of change and acceptability of programming.

**Table 1 Tab1:** Key study characteristics by COMPASS country site

Site	Primary research question	Study design	Quantitative surveys	Quantitative sample size at baseline
Conflict-affected communities in Kabare and Uvira territories, South Kivu Province, Democratic Republic of Congo	What is the incremental effectiveness of the parental curriculum, in addition to the core COMPASS programming, on improving girls’ safety and well-being?	Wait-list cluster randomized controlled trial + qualitative	10-12 year old CAPI survey^a^	886 girls (10–14 years)
			13-14 year old CAPI + ACASI survey	777 primary caregivers for girls
			Caregiver survey	
Refugee camps (Sherkole, Tongo, and Bambasi), Benishangul-Gumuz Region, Ethiopia	What is the overall effectiveness of the COMPASS program on improving girls’ safety and well-being, as compared to girls in the wait-list arm?	Wait-list cluster randomized controlled trial + qualitative	13-19 year old ACASI survey	919 girls (13–19 years)
Communities, and Jalozai camp in Khyber Paktunkwah Province, Pakistan	What is the overall acceptability and feasibility of COMPASS programming?	Pre-post test + qualitative	12-19 year old paper-based survey	208 girls (12–19 years)

^a^The 10–12 year old survey does not contain sensitive questions of sexual health

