**Fig 1 Fig1:**
[figure not shown]
Theory of Change for COMPASS

Caregivers will also participate in monthly discussion groups which seek to increase knowledge of the needs of adolescent girls. The goals are to ultimately shift gender-inequitable attitudes about girls in the home and increase support to keep girls safe within and outside of the home. This content is delivered by IRC program staff. The incremental effectiveness of this caregiver component is being tested in DRC, while in Ethiopia we are evaluating the overall COMPASS program effectiveness.

In addition, COMPASS will engage health service providers and case managers to train workers on Clinical Care for Sexual Assault Survivors [28] and Caring for Child Survivors Guidelines [29] in order to improve the overall quality of services for adolescent girl survivors of violence in their communities. Additional activities will be undertaken to engage communities to support girls as well.

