Other biases have been considered in the study design as well. Primarily, contamination is of concern as intervention groups and wait-listed groups may interact with each other which may minimize our ability to detect changes between groups. Due to sample size requirements for cluster-randomized controlled trials, groups were randomized within communities in DRC and within small geographical areas in refugee camps in Ethiopia. Potential contamination will be assessed during the endline data collection. Social desirability bias may also emerge if respondents in the intervention arm report lower levels of violence, for example, to please the interviewer. However, the use of ACASI may minimize this bias as interviewers will not be aware of the girls’ responses. In addition, another concern is that humanitarian settings are comprised of highly mobile populations, such that girls and caregivers may move out of the study area during the period of program delivery. Attendance will be tracked and intention-to-treat and per-protocol analyses will be undertaken to assess how this attendance may impact the effectiveness of COMPASS. Finally, behavior change to reduce violence against women and girls may require long term investments and our ability to see changes in the limited follow-up period may be minimized. Therefore, examination of secondary outcomes, such as gender attitudes and norms will also be critical to interpretation of the effectiveness of COMPASS as well as the potential salience of different pathways to change. As seen in other community-based trials to reduce intimate partner violence, consistency, trends, and alignment with hypothesized directions of change of both primary and secondary outcomes will be examined to provide insight into potential effectiveness [19, 20, 36, 37].

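### The Ethiopia arm contrast estimates safe-space sessions plus caregiver groups on top of camp-wide activities, not the overall COMPASS effect that the research question names

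*Protocol article*

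**What the plan says.** All places are in the protocol article.

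- **Question.** Table 1 (Study design) gives the Ethiopia question as "What is the overall effectiveness of the COMPASS program", with girls in the wait-list arm as the comparator. The Intervention description repeats it: "in Ethiopia we are evaluating the overall COMPASS program effectiveness". The Abstract also speaks of overall impact against a wait-list group.
- **What COMPASS contains.** The Abstract (Methods/design) lists facilitated sessions in safe spaces together with "caregiver discussion groups, capacity-building activities with service providers, and community engagement".
- **Level of the last two components.** The Intervention description says that "COMPASS will engage health service providers and case managers to train workers", in order to "improve the overall quality of services for adolescent girl survivors of violence in their communities". A further sentence there promises extra work with communities. Neither activity is assigned to an arm.
- **Randomisation.** Under Randomization, sample size, and power analysis, 47 girl groups across three camps are stratified by age and allocated to intervention or wait-list. The Discussion adds that "groups were randomized within communities in DRC and within small geographical areas in refugee camps in Ethiopia".
- **Contamination.** The Discussion treats this as contact between intervention and wait-list groups, which could make differences harder to detect, and plans to assess it at endline.

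**The concern.** A randomised comparison estimates the effect of what differs between the arms. If health workers and case managers are trained for a camp, and community work is done across it, girls in both arms live with the result. Those components then do not differ between the arms, and their contribution to girls who attend no sessions cancels out of the comparison.

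What is at stake is the conclusion. A positive result would be reported as the effect of COMPASS as a whole, when it is the effect of two components in camps that already have the other two. A null result could be read as evidence that the package does not work, although the trial has no comparison that shows what the camp-level components contribute. The article draws this kind of distinction for DRC, where the question is explicitly the increment from the caregiver component, but not for Ethiopia.

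**Working it through.** **Step 1. The plan's own figure.** Inputs from Randomization, sample size, and power analysis: d = 0.3 between treatment and wait-list, 80% power, alpha 0.05 (taken as two-sided; sidedness is not stated), design effect 2.0.

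- Per arm before clustering: 2 × (1.960 + 0.842)² / 0.3² = 174.4, so 175.
- Total: 175 × 2 arms × 2.0 = 700, against 704 stated.
- With 176 per arm, 176 × 2 × 2.0 = 704 exactly, and power is 0.804.

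The figure reproduces, so the point does not rest on a sample-size error.

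**Step 2. Components against arms in Ethiopia.**

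| Component | Level described | Differs between arms? |
|---|---|---|
| Safe-space sessions | Girl group, the randomised unit | Yes |
| Caregiver groups | Caregivers of participating girls | Yes (assumed to follow the girl's arm) |
| Service-provider training | Services in girls' communities | No restriction to an arm stated |
| Community engagement | Communities | No restriction to an arm stated |

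Because allocation takes place inside small areas of the camps, a trained provider or a community activity in an area serves girls of both arms unless something is done to prevent it. The article describes no such step.

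**Step 3. What the contrast estimates.** Write Y(s, c) for the mean outcome with (s = 1) or without (s = 0) sessions and caregiver groups, and with (c = 1) or without (c = 0) the camp-level components.

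- Full-package effect: Y(1,1) − Y(0,0).
- Arm contrast, if both arms have c = 1: Y(1,1) − Y(0,1).
- Difference between the two: Y(0,1) − Y(0,0), the effect of the camp-level components on girls without sessions.

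If that last term is beneficial, the contrast is smaller than the package effect. If effects are additive and the shared components carry a fraction f of the total, the contrast equals (1 − f) times the package effect, and the whole contribution of the shared components drops out. Without additivity, any part that works only through session attendance, such as referral by a mentor, stays in the contrast.

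The article gives neither f nor anything from which to derive it. More girls would not close the gap, because it is a difference in the quantity estimated, not in precision.

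**The case against.** **Shared exposure is inferred.** No sentence says that wait-list girls receive the camp-level components, and an article may leave roll-out detail to the full protocol. This stands as a limit on certainty. But the components, their level, the unit and place of randomisation and the research question are all stated here, and as stated they do not fit together.

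**Overall can be read more loosely.** Set against the incremental question in DRC, it may mean the bundle offered to intervention girls, and Table 1 names the wait-list as comparator. That is a fair reading of intent. Yet the bundle is defined to include provider training and community work, and naming the comparator does not tell the reader that it is probably exposed to part of the programme.

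**The shared part may be small.** Provider training mainly concerns care after violence, whereas the primary outcome is past-year sexual violence. The safe-space work is called the core component, and Study settings shows that survivor services and community mobilisation already existed in the camps. All of this bears on the size of the gap and is a reason not to put a number on it.

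**It is partly handled.** The Discussion discloses within-area randomisation and plans an endline check of contamination. Monitoring and process evaluation covers provider quality and is meant to help explain results. Contact between girls is a different mechanism from joint exposure to an activity, however, and neither passage narrows the question.

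**A stronger reading to avoid.** A reader might infer that the trial is underpowered: if 20%, 30% or 40% of an overall d = 0.3 were shared, the contrast would be 0.24, 0.21 or 0.18 and power 61%, 50% or 39%. The document does not support this. It defines d = 0.3 between treatment and wait-list groups, which is already the contrast the trial makes, and does not rest it on an untreated comparator. Those shares have no source in the text.

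**Conclusion.** The point holds as one of labelling and interpretation. On the most natural reading, the Ethiopia trial validly estimates the effect of safe-space sessions plus caregiver groups in camps where provider training and community engagement are also under way. It does not estimate the effect of the full package.

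The conclusion rests on two assumptions: that the camp-level components were not withheld from wait-list girls, and that caregiver groups follow the girl's arm. The direction, understatement of the package effect, further assumes that the shared components are beneficial and roughly additive. The amount cannot be quantified from the document and could be small.

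The randomised comparison and the planned 704 girls are not in question. A reader might go further and infer that the trial is invalid, or that shared exposure is established fact; the text supports neither.

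**What to change.** Restate the Ethiopia question, in the Abstract, Table 1 and the Intervention description, as the effect of safe-space sessions plus caregiver groups over and above camp-wide service-provider training and community engagement. Word the planned conclusion the same way. Add to the Discussion that the trial does not estimate the effect of the full package, and that a null result would not show the full package to be ineffective.

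If some camp-level components were in fact withheld from wait-list girls, say which ones and how this was done within shared areas. The question can then keep a correspondingly wider wording.

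The cost is a few sentences and a narrower claim. Randomisation, sample size, data collection and conduct do not change.

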### Study settings

Eastern DRC has grappled with protracted conflict for decades, vacillating between periods of relative calm and instability. North and South Kivu provinces in eastern DRC are home to approximately 60 % of DRC’s 2.6 million internally displaced persons as well as continual influxes of refugees from Burundi, Rwanda, or other neighboring countries [24]. Violence against women in eastern DRC is widespread, as up to 40 % of women report lifetime experience of sexual violence [25, 26]. While less is known about the experiences of adolescent girls in eastern DRC, non-representative monitoring data from IRC partners documented an increase from 12 % to 28 % of girls aged 12–17 years among their caseloads of survivors between January and September 2012 during outbreaks of violence. At study inception, COMPASS was planned to take place in both North and South Kivu, yet, given unpredictable outbreaks of violence and security concerns for program and research staff in North Kivu, the study setting was refined to take place in fourteen communities in Kabare and Uvira territories, South Kivu. IRC has been operating in eastern DRC since 1996 and has been running a large and comprehensive program to protect and empower women and girls. This program includes health care and case management for survivors, capacity-building activities with community-based organizations, socio-economic activities and primary prevention interventions, in addition to general emergency response programming.

Three refugee camps in the Benishangul-Gumuz region of Ethiopia, bordering Sudan and South Sudan, serve as the second study site. Approximately 38,000 people reside in these three primarily Sudanese refugee camps (Sherkole, Tongo, and Bambasi), which are characterized by multiple safety and protection concerns. Documented in the IRC Community Wellbeing Initiative (CWI) programming assessments, concerns include high risks of adolescent girls experiencing sexual violence prior to arrival in Ethiopia and early or forced marriage. Often, these marriages are seen as a mechanism to ‘protect’ girls from sexual violence or as a means for girls’ to meet their basic needs [27]. These camps, established in 2011–2012, are highly diverse with numerous ethnicities of refugees and languages spoken. IRC has been operating in these camps since 2014 and provides community well-being programming, health programming, and water/ sanitation services, amongst other programs. Specific CWI programming includes providing access to quality health, psychosocial, and legal protections for survivors of gender-based violence, and community mobilization activities across the refugee camps.

### Intervention description

The theory of change for the COMPASS program is presented in Fig. 1. The core component of the program is to provide opportunities for girls to build assets to protect against and respond to violence and establish a foundation for a healthy transition to adulthood through mentorship, learning, and peer interaction in safe spaces. A specific activity through which this may be achieved is through the implementation of structured, facilitated sessions that focus on topics, tailored for girls, such as self-confidence, building friendships, communication, problem solving, puberty and reproduction as well gender based violence and creating healthy relationships. All of the above are aimed at helping girls prepare for making decisions about adult relationships, including their ability to negotiate sex, and understand their self-worth. In addition, adolescents are asked to create plans to minimize risk of entering relationships where girls may experience abuse, violence, or exploitation. This curriculum has been adapted for age groups in the study and settings, and will be delivered by young female mentors (from their late teens to 30 years old) trained by IRC COMPASS program staff. Over the course of 10–12 months, activities will be delivered in safe spaces for girls: specially constructed *tukuls* (i.e., traditional huts) in Ethiopian refugee camps for only women and girls, and dedicated spaces in community based women’s organizations in DRC. These safe spaces were developed specifically for girls through several community and caregiver consultations.

